## Abstract

**Introduction:**

Bereaved parents, who have lost a child, have an elevated risk to develop mental health problems, yet, few studies have evaluated the effect of psychosocial interventions developed for bereaved parents. Cognitive–behavioural therapy (CBT), both face to face or digitally delivered, has shown to be an effective intervention for prolonged grief symptoms. Self-help mobile apps offer various advantages and studies show improved mental health after app interventions. No app has yet been evaluated targeting prolonged grief in bereaved parents. Therefore, the aim of this planned study is to develop and examine the effectiveness of a CBT-based mobile app, called *My Grief,* in reducing symptoms of prolonged grief, as well as other psychological symptoms, in bereaved parents. Another aim is to assess users’ experiences and adverse events of *My Grief*.

**Methods and analysis:**

We will conduct a two-armed randomised waitlist-controlled trial. Parents living in Sweden, who lost a child between one and ten years ago, with elevated symptoms of prolonged grief, will be recruited to participate in the trial. The content of *My Grief* covers four main domains (Learn; Self-monitoring; Exercises; Get support) and builds on principles of CBT and the proven-effective *PTSD Coach* app. Participants in the intervention group will fill out online questionnaires at baseline and at 3, 6 and 12 months follow-ups, and the waitlist-controls at baseline and at 3 months. The primary outcome will be prolonged grief symptoms at the 3 months follow-up. Secondary outcomes are post-traumatic stress and depression symptoms, quality of life and cognitive behavioural variables (ie, avoidance, rumination, negative cognitions).

**Ethics and dissemination:**

Ethical approval has been received from the Swedish Ethical Review Authority (project no. 2021-00770). If the app is shown to be effective, the app will be made publicly accessible on app stores, so that it can benefit other bereaved parents.

**Trial registration number:**

NCT04552717.

Strengths and limitations of this studyThis is the first study to examine whether access of a self-help app can have beneficial effect on bereaved parent’s mental health and quality of life.This study will examine the effect of the app on cognitive behavioural processes proposed to underlie the development of prolonged grief.Generalisability of findings from this study may be limited as parents who want to participate in such study may experience fewer barriers to talk about the loss and seek help for their grief.This study includes parents who have lost a child, hence the findings may not be generalisable to other types of loss.This study uses self-report questionnaires, hence we do not establish formal diagnosis of prolonged grief disorder.

## Introduction

The death of one’s child can be a traumatic life experience and bereaved parents are at increased risk of developing both mental and physical health problems.^1–6^

While most bereaved individuals adjust to the loss of a loved one without professional intervention, a significant minority experience a persistent, severe and disabling grief reaction, called prolonged grief. Prolonged Grief Disorder (PGD), a diagnosis characterised by such severe grief responses, was recently included in the International Classification of Disorders eleventh edition.^7^ A similar version of PGD is scheduled to be included in the text revision of fifth edition of the Diagnostic and Statistical Manual of Mental Disorders (DSM-5-TR; for a commentary see Boelen *et al*^8^). Across both disorders, core symptoms are persistent and pervasive yearning for the deceased, persistent and pervasive cognitive preoccupation with the deceased, as well as accessory symptoms presumed indicative of intense emotional pain, such as difficulty accepting the loss, a feeling that one has lost a part of one’s self, and difficulty in engaging in social activities. Such severe grief reactions often co-occur with, yet are distinct from, disorders such as depression and post-traumatic stress,^9^ and relate to suicidal ideation,^10^ as well as reductions of quality of life.^11^

Bereaved parents are at high risk to develop prolonged grief.^12–14^ For example, 16% of cancer bereaved parents may have reactions indicative of PGD.^15^ Yet, there is a lack of studies evaluating the effect of psychosocial interventions for bereaved parents.^16 17^ Thus, the development and evaluation of accessible interventions to prevent and reduce negative mental health consequences after child loss appears clinically important.

A growing body of evidence shows that cognitive–behavioural therapy (CBT) is effective in treating prolonged grief symptoms when delivered face to face^18–21^ or via internet.^22–24^ Briefly, the cognitive behavioural model of prolonged grief proposes that three core processes explain the occurrence and persistence of grief symptoms: insufficient integration of the loss with existing autobiographical knowledge; negative global beliefs about oneself, the world, and the future and catastrophic misinterpretations of grief symptoms; and anxious avoidance (ie, cognitive and overt avoidance of reminders of the loss) and depressive avoidance (ie, avoidance of social, occupational and recreational activities, and behavioural withdrawal).^25^ Accordingly, CBT treatments of prolonged grief typically includes creating a coherent, meaningful autobiographical narrative about the loss; challenging negative beliefs and catastrophic misinterpretations through cognitive restructuring; gradually confronting persons in vitro or in vivo with avoided aspects of the loss (eg, places, objects, memories) through exposure techniques; and/or helping people to set new life-goals and engage in new, meaningful activities.^26^ Increasingly, researchers are also focused on examining the efficacy of other, complementary therapeutic techniques, which may be helpful in reaching these treatment goals, such as mindfulness-based therapy and relaxation.^27–29^

Mobile apps offer additional advantage over face-to-face and web-based interventions because of their availability, accessibility, the immediate support they can provide, and their anonymity (eg, reducing barriers to seeking help for grief), low costs and possible tailoring to the user (eg, the user are in control over when and how to use the app).^30^ Most individuals own a smartphone, regardless of socioeconomic background or living conditions, and many spend 2–5 hours a day using their smartphone.^31^ Moreover, people with mental health issues report daily use of smartphones to connect to other people and search for health-related information.^32 33^ Hence, mobile apps have a great potential to be used as self-help interventions for mental health problems. Indeed, various mobile apps for mental health have shown to be effective.^34 35^ Treatment trials have shown that mobile apps can decrease a variety of psychological symptoms, including post-traumatic stress^36 37^ but also depression,^38^ anxiety^39^ and substance use (eg, tobacco, alcohol and drugs).^40^

Despite the availability of a large number of mobile apps in app stores that claim to improve mental health, empirical evidence is lacking for most mobile applications.^30 34 35^ To our knowledge, no evidence-based app to reduce grief for bereaved parents exists. Based on the existing knowledge, we believe an app targeting prolonged grief using elements of CBT could potentially be effective in improving mental health in bereaved parents.

The general goal of the present intervention study is to evaluate the effectiveness of an app for bereaved parents, which aims to facilitate the grieving process. The intervention includes access to a self-management mobile app, called *My Grief*, and is based on the cognitive behavioural conceptualisation framework of prolonged grief.^18 25^ The intervention also includes other evidence-based techniques from CBT such as elements of mindfulness and deep muscle relaxation practices, as these techniques have shown promising effects on loss-related mental health for bereaved individuals.^27^

The main aim of this study is to examine the effectiveness of the app *My Grief* as compared with a waiting list comparison in reducing symptoms of prolonged grief in bereaved parents. The primary hypothesis is that the parents in the intervention group will report decreased levels of prolonged grief symptoms after having access to the app. A second aim is to examine the effect of the app on related mental health problems (post-traumatic stress symptoms, depression symptoms and quality of life) and cognitive behavioural variables putatively explaining the effect of CBT techniques (ie, grief avoidance, grief rumination and negative grief cognitions). The secondary hypotheses are that the parents in the intervention group will report improved mental health (ie, lower symptom levels of depression and post-traumatic stress, higher quality of life) and lower grief avoidance, grief rumination and negative grief-related cognitions. A third aim is to assess participants experience of using the app, for example, perceived satisfaction helpfulness and adverse events.

## Methods and analysis

### Design

We plan to conduct a two-armed parallel-group randomised waitlist-controlled trial comparing the effects of access to the *My Grief* for 3 months compared with waitlist. An external statistician will generate the allocation sequence: a random number table with equal allocation to access to *My Grief* or waitlist (1:1) with an unstratified, block design fixed at 20 allocations. The first author will upload the random number table, without reviewing it, into the Research Electronic Data capture (REDCap) randomisation tool prior to data collection. Randomisation will take place after the pre-assessment is completed. When both parents of a deceased child participate, the second parent taking part will be manually assigned to the same group as the first parent is assigned to through randomisation. Participants will be informed of group allocation immediately after randomisation (figure 1).

**Figure 1 F1:**
[figure not shown]
Design of the randomised controlled trial.

### Participants and procedures

Parents living in Sweden, who lost a child between 1 and 10 years ago, with elevated symptoms of prolonged grief, will be recruited to participate in the intervention.

The recruitment comprises two different procedures, (1) potential participants are identified using the Swedish Childhood Cancer Registry, the Cause of Death Registry, and the Swedish Population Register at the Swedish Tax Agency. By linking the Cause of Death Registry with the Swedish Childhood Cancer Registry, children diagnosed with a malignancy and who died 1–10 years previously will be identified. Thereafter, the children’s parents are identified through the Swedish Population Register and will be sent a letter with an invitation to participate in the study. (2) Parents will also be recruited from non-profit organisations for bereaved parents who have lost a child (Vi Som Förlorat Barn and the Swedish Childhood Cancer foundation) via their social media sites and newsletters. People who are interested in participation, from both recruitment procedures, are directed to a website, www.minsorg.com, where they can access information about the study aims and procedures. On the website, they can sign up to the study and complete an online screening questionnaire which automatically direct eligible participants to an informed consent form and the pre-assessment online questionnaire, in REDcap.^41^ After filling in the pre-assessment participants are randomised to either the intervention or waiting list group. Participants in the intervention group will receive a phone call from a researcher 1 week after the intervention started to ensure that the app is working properly. Participants in the intervention group are allowed to use the *My Grief* app for 3 months. The control group will be informed that they are on the waiting list and will be offered access to the *My Grief* app after 3 months (figure 1). Recruitment is planned to start August 2021.

### Eligibility criteria

Inclusion criteria for participation are: (1) being a parent of a child who has died between 1 and 10 years previously, (2) having elevated symptom levels of prolonged grief (Prolonged Grief Disorder-13, (PG-13), cut-off >16), (3) understanding and speaking Swedish and (4) having access to a smartphone. Exclusion criteria are self-reported ongoing suicidal thoughts or psychosis, assessed with single items in the screening questionnaire.

### Sample size

A required sample size of 154 participants was calculated in G*Power V.3.1, based on the primary research question. We considered a moderate effect size to be clinically meaningful (*f*=0.25), within a repeated measure analysis of variance, a desired power of 0.80, *α*=0.05, and an assumed strong association (*r*=0.50) between the preassessment and postassessment. The estimate includes an anticipated attrition rate of 16%.^42^

### Intervention

*My Grief* is a self-help app for smartphone users, compatible with both iOS and Android. The app builds on principles of CBT and a PGD online-treatment protocol.^43^ It is based on a cognitive‐behavioural conceptualisation of prolonged grief and proposes that three ‘grief tasks’ are critical in alleviating grief.^18 25^ These tasks are (1) facing the loss and the pain that goes with it, (2) keeping confidence in yourself, others, life and future, and (3) engaging in helpful activities that promote adjustment to the new situation. Interventions used to accomplish these tasks include psychoeducation and normalisation of grief reactions, exposure to avoided aspects of the loss, and goal setting and behavioural activation. The structure of the app includes four main sections (figure 2) and is based on *PTSD Coach* app with permission from the Veterans’ Affairs National Center for PTSD and Department of Defense’s, Defense Health Agency, Connected Health (PTSD, Post Traumatic Stress Disorder).^36 44^

**Figure 2 F2:**
[figure not shown]
Structure of the *My Grief* app.

The four main sections in *My Grief* include:

#### Learn

This section provides psychoeducation about grief. It covers what is normal- and prolonged grief; what commonly experienced thoughts, feelings and behaviours are after loss; the three grief tasks and coping with grief within the family. The latter topic includes tips on how to understand different family members’ grieving processes, how to help each other, how to continue doing things together, how to support the remaining children in the family (ie, siblings to the deceased child) in their grief process, and how to talk to children about death. In each part, there are links to corresponding exercises in section 3.

#### Self-monitoring

This section includes a rating scale (score 0–10) that users can employ to assess the daily intensity of their grief and the highest and lowest grief levels during the day. It also provides space to note what happened at that time. The section gives users both visual and written feedback from themselves as the results are presented together with previous assessments. This enables users to monitor their grief intensity and symptoms over time, to recognise situations when grief levels are low or high, and to identify activities and internal and external stimuli associated with increases and decreases in grief; this helps them to learn more about one’s own grief and to improve adaptive ways of coping. User can use the rating scale as many times as they want, whenever they want. Participants are encouraged to fill in the scale daily and they can choose to receive a daily reminder to fill in the scale.

#### Exercises

This section provides the user with self-guided exercises. A majority of the exercises include recorded audio messages. For example, the user can choose to read or listen to instructions for a particular exercise. Some of the exercises were taken from the *PTSD Coach Sweden*,^45^ including mindfulness exercises (eg, body scan, mindful breathing, learning to be aware of one’s senses), progressive muscle relaxation, deep breathing, and stress reduction and positive psychology exercises. Other exercises were derived from CBT.^18 25^ The writing exercise section includes tasks covering the three grief tasks in the CBT model. Three writing exercises, drawing from an internet-based exposure treatment,^43^ are related to task one. In these writing exercises, participants expose themselves to the story of loss and are encouraged to confront implications of the irreversibility of the separation from the deceased. For example, in the exposure to the story of the loss the participants are instructed to write down what happened around the time of the death, in three steps, in order to confront feelings, thoughts, and situations which are difficult and emotionally painful. One exercise is related to grief task two and instructs participants to take a few minutes every day to think positive about the future and what they want for the future and to write this down in a diary. One exercise related to grief task three, is based on behavioural activation principles. It consists of encouragement to plan a moment every day to engage in an activity that potentially elicits some pleasure or joy.

#### Get support

This section provides the user with contact details to different support functions and help-lines (including phone numbers, chats, email addresses, and websites) for both the parent and his/her family members. These support functions or help-lines include the Childhood Cancer Foundation, a suicide prevention organisation, and different networks and non-profit organisations for parents who lost a child. It also includes psychoeducation regarding how the user can create and expand one’s own support network throughout reaching out for help to family and friends. Participants can create a list of phone-numbers to family, friends and help-lines in this section as well.

### Data collection

Participants complete questionnaires online. Time points for data collected via online questionnaires at t0 (baseline), t1 (3 months), t2 (6 months, only intervention group) and t3 (12 months, only intervention group) (table 1; figure 1). If the participant has not completed the online questionnaire, two reminder emails will be sent out for each measurement time point.

**Table 1 T1:** Time points for measurements

	Before baseline	t0, baseline	t1, 3 months	t2, 6 months*	t3, 12 months*
Consent	X				
Screening	X				
Sociodemographic		X			
Prolonged grief (Prolonged Grief Disorder-13)		X	X	X	X
Post traumatic stress (Post-traumatic Stress Disorder Checklist-5)		X	X	X	X
Depression (Patient Health Questionnaire-9)		X	X	X	X
Quality of life (Brunnsviken Brief Quality of Life Inventory)		X	X	X	X
Grief avoidance (Depressive and Anxious Avoidance in Prolonged Grief Questionnaire)		X	X	X	X
Grief rumination (Utrecht Grief Rumination Scale)		X	X	X	X
Negative grief cognitions (Grief Cognition Questionnaire-18)		X	X	X	X
Users’ experiences*			X		

*Only intervention group.

#### Sociodemographic and loss-related variables

A self-constructed questionnaire will be used to gather information about the participants’ demographic information, such as age, gender, education, employment, the child’s diagnosis (if applicable), cause of death and date of the child’s death. These data will be used to describe the sample.

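### The condition-by-time model leaves precision unused: adjusting the 3-month analysis for the baseline score, and for time since loss, would be a nearly free improvement

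*Protocol article*

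**What the plan says.** All places are in the protocol article.

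- **Statistical methods and analysis.** Primary and secondary outcomes are analysed by regression with the direct effects and the interaction of condition and time, with the primary endpoint at 3 months. No further covariate is named and none is excluded. The between-group effect size divides the difference in change scores by the pooled baseline SD. All randomised participants are included, and missing follow-up is treated as missing at random.
- **Sociodemographic and loss-related variables.** The questionnaire collects items such as "age, gender, education, employment, the child’s diagnosis (if applicable), cause of death and date of the child’s death". Their one stated purpose is: "These data will be used to describe the sample". Recruitment route is not among the items named.
- **Design.** Allocation is 1:1 with an "unstratified, block design fixed at 20 allocations". When both parents of a child join, "the second parent taking part will be manually assigned to the same group as the first parent".
- **Participants and procedures; Eligibility criteria.** "The recruitment comprises two different procedures": registry linkage with a letter, and non-profit organisations. Eligibility requires "being a parent of a child who has died between 1 and 10 years previously".
- **Sample size.** 154 participants, from f = 0.25, power 0.80, α = 0.05, r = 0.50 between pre- and post-assessment, and 16% attrition.

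**The concern.** Baseline PG-13 and the date of death will be known for every randomised parent before allocation. The stated model uses the baseline score only as the first of two time points, and it does not use the date of death.

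Subtracting the baseline in full is less efficient than letting the regression estimate its weight whenever the pre-post correlation is below 1, and the plan assumes 0.50. Time since loss spans a tenfold range and may relate to how grief moves over 3 months, so it could explain some of the remaining variation.

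What is at stake is the width of the interval around the treatment effect. If adjustment is not written down now, adding it after an imbalance has been seen would look post hoc.

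**Working it through.** **Inputs.** N = 154, 16% attrition, f = 0.25, α = 0.05, power 0.80 and r = 0.50 (Sample size); the model terms (Statistical methods and analysis). Equal SDs at the two time points are assumed, and d is in units of that SD. The partial R² of time since loss is not in the article; 0.02 to 0.10 is assumed.

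**1. The plan's figure.** For two groups, d = 2f = 0.5. A non-central F test with λ = f²N and 1 and N − 2 degrees of freedom first reaches 0.80 at N = 128 (power 0.8015). Then 64 / 0.84 = 76.2, rounded up to 77 per arm, or 154 in total: reproduced. The figure fits a change-score comparison, because with r = 0.50 the change score has variance 2(1 − 0.50) = 1, the same as a single measurement. The expected number analysed is 154 × 0.84 ≈ 129.

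**2. What the interaction estimates.** With baseline and 3 months only, and complete data, the condition-by-time coefficient is the mean change in the app arm minus the mean change in the waitlist arm.

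**3. Residual variance, in units of SD².**
- Change score: 2(1 − r) = 1.00.
- Baseline as covariate: 1 − r² = 0.75.
- Ratio: (1 + r)/2 = 0.75, a 25% reduction. For illustration, r = 0.3 gives 0.65 and r = 0.7 gives 0.85.

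**4. Power at d = 0.5 with 64.5 per arm.** The formula is Φ(0.5 / (s√(2/64.5)) − 1.96), where √(2/64.5) = 0.176.
- Change score, s = 1: 0.5/0.176 = 2.84, and Φ(0.88) = 0.81.
- Baseline-adjusted, s = √0.75 = 0.866: 0.5/0.1525 = 3.28, and Φ(1.32) = 0.906.

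Simulation of the baseline-adjusted analysis (128 analysed, 4,000 trials per setting) gave 0.897 to 0.907, hence about 0.90. By the normal formula, the total needed for 80% power before attrition is 126 for the change score and 96 with baseline as covariate.

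**5. Adding time since loss.** Residual variance is multiplied by (1 − R²), with R² assumed.

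| Partial R² | Power, change score | Power, baseline-adjusted |
|---|---|---|
| 0 | 0.810 | 0.906 |
| 0.02 | 0.818 | 0.912 |
| 0.05 | 0.830 | 0.920 |
| 0.10 | 0.849 | 0.933 |

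On top of baseline adjustment the gain is 0.6 to 2.7 points. In simulations where time since loss and route together carried the R², power moved from 0.897 to 0.903 (R² = 0.02) and from 0.900 to 0.918 (R² = 0.10).

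**6. Where the covariate must go.** With complete data, adding a time-invariant variable as a main effect to the condition-by-time model leaves the interaction estimate unchanged. The gain needs a 3-month outcome model, not one more term in the present model.

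**7. Validity without adjustment.** Simulated type I error without the two loss covariates was 0.048 to 0.051. At 77 per arm, a 50:50 factor differs between arms with SD √(0.25 × 2/77) = 0.081. A gap above 10 percentage points has probability 0.22, or 0.31 if same-arm couples inflate the variance by an assumed factor of 1.5. A 10-point gap on a factor worth an assumed 0.3 to 0.5 SD moves the estimate by 0.10 × 0.3 = 0.03 to 0.10 × 0.5 = 0.05 SD, against a standard error of about 0.18 SD. The simulation treated parents as independent; within-couple correlation is a separate matter.

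**The case against.** The best counter-argument is scope. A journal article condenses the plan, and covariate lists usually sit in the full protocol or SAP. The model statement rules nothing out, and no figure is wrong. This stands to the extent that the point is an improvement and not an error. It does not remove the point, because the article names the model terms, defines the between-group effect on change scores and assigns the loss data a purpose. Read together, these describe a specific and less efficient analysis. If the full plan uses a longitudinal model with a common baseline mean, much of the gain in step 4 is already secured and should be stated.

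A reader might go further and infer that unstratified randomisation over two routes and a 1 to 10 year span leaves chance imbalance to distort the result. The documents do not support that:

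- Randomisation keeps the test valid, and unstratified blocks are an acceptable choice at this size. Same-arm couples share date and cause of death, which makes imbalance on those factors somewhat likelier but does not bias the comparison.
- Stable differences in grief level by time since loss or route cancel in the change contrast. Only differences in course over 3 months could matter, and the article gives no evidence on these.
- The article states a descriptive use for the loss data; it does not say that this is their only use.
- Route is not listed as recorded, and both routes lead to the same website. Cause of death is a poor proxy for route, because one of the two organisations is a childhood cancer foundation.

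**Conclusion.** The point holds as a free improvement. The planned analysis is valid but gives up precision that data already collected could supply. The well-supported part is baseline adjustment: 25% less residual variance than a change-score contrast, and power of about 0.90 in place of 0.81 at d = 0.5 with about 129 analysed. This rests on the plan's own r = 0.50, on equal SDs at the two time points, and on reading the model as a change-score contrast. The further 1 to 3 points from time since loss rest on an assumed partial R² of 0.02 to 0.10; if its true value is zero, there is no gain. The point gives no reason to change the sample size or the randomisation.

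**What to change.** 1. In Statistical methods and analysis, state that the treatment effect on the primary outcome is the between-arm difference in PG-13 at 3 months, adjusted for baseline PG-13 and time since loss (continuous). State the same for each secondary outcome, with that outcome's own baseline value. Retain all randomised participants and the missing-at-random assumption.
2. In Sociodemographic and loss-related variables, add that the date of death also supplies time since loss as a prespecified covariate.
3. Include recruitment route as a covariate only if it is recorded for every participant.
4. For consistency, take the adjusted difference as the numerator of the between-group effect size and keep the pooled baseline SD as the denominator.
5. Leave the randomisation unchanged.

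The cost is one or two degrees of freedom out of about 129 analysed, or one more if route is included. Baseline scores and time since loss need no new data collection. The model statement has to be rewritten, because adding a main effect to the present model would achieve nothing.
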